# INVESTIGATIONAL MEDICINAL PRODUCT

## Name and description of investigational medicinal product(s)

Remifentanil (Ultiva®)

Ropivacaine (Naropin®)

Sufentanil (Sufenta®)

## Summary of findings from clinical and non-clinical studies

Remifentanil, is a new synthetic opioid (anilidopiperidine) with direct agonist action specifically on mu-opioid receptors (7). The rapid onset and offset of the drug make remifentanil very suitable for administration via patient controlled analgesia (PCA).

Remifentanil is used as an analgesic agent for use during induction and/or maintenance of general anesthesia. It is also used as PCA in postoperative patients. Indications, contra-indications, farmacodynamic properties and possible side effects are described in the SmPC (Summery of Product Characteristics) of remifentanil/ Ultiva®(24).

Remifentanil PCA can be used for analgesia during labor. Placental transfer of remifentanil does occur but appears to be rapidly metabolized, redistributed, or both. There were no adverse neonatal or maternal effects, only mild maternal sedation and respiratory changes (8). There have been multiple clinical studies on the use of remifentanil in the parturient (9-21). In our unpublished data (pilot study and STER study), 100 women received RPCA and only in one case medication had to be stopped because of serious side-effects (decrease in respiratory rate).

In epidural analgesia low concentration of local anesthetic (ropivacaine) with opiates (sufentanil) is administered via continuous infusion in the epidural space. Reported maternal complications include hypotension, itching, drowsiness and fever. Also accidental punctuation of the dura which can result in post-dural headache. Epidural analgesia can also influence the course of labor (2).

## Summary of known and potential risks and benefits

Already documented risk of remifentanil PCA are maternal respiratory depression, nausea/vomiting and itching. Known risks of epidural analgesia are hypotension, increased use of oxytocin and increased risk of instrumental delivery.

## Dosages, dosage modifications and method of administration

Remifentanil patient controlled analgesia, intravenous administration; 30 microgram boluses, lockout time 3 minutes, maximum dose limit 1200 microgram/hour. It is possible to increase the bolus dosage to 40 microgram in case of insufficient pain relief, or to decrease the dose to 20 microgram in case of signs of respiratory depression or sedation.

Epidural analgesia, epidural administration according to local protocol. Suggested protocol: loading dose of 25 mg (12.5 ml ropivacaine 0.2%), continuous infusion of ropivacaine 0,1% plus sufentanil 0,5 microgram/mL.

# METHODS

## Study parameters/endpoints

### Main study parameter/endpoint

### The main outcome parameter is pain appreciation. Women will be asked to express their level of satisfaction with pain from the start of labor hourly and after start of pain relief every 15 min during the first hour and hourly after that. This will be scored on a visual analogue scale (VAS) ranging from 1 (highly dissatisfied) to 10 (highly satisfied). Total pain relief (TOTPAR) is a time weighted measure of area under the curve (AUC) or total area under the pain appreciation curve and is a summary measure that integrates serial assessments of a subject’s pain appreciation over the duration of the study.

### Secondary study parameters/endpoints

If RPCA is equivalent to EA with respect to pain appreciation the next endpoint will be the costs of both interventions. For both strategies the cost of perinatal care for mother and child, starting at the onset of labor and ending ten days after delivery, will be registered and compared (without discounting). The costs consist of costs of delivery/childbirth (course and mode of delivery), postnatal maternal care (hospitalization, outpatient visits), neonatal care (admission to NICU/neonatology ward, outpatient visits) and primary care (midwife, general practitioner, maternity care).

Maternal outcome

- Morbidity (post spinal headache, postpartum haemorrhage (>1 litre or administration of blood products), uterine rupture, eclampsia, amniotic fluid embolism, myocardial infarction, admission to ICU, other (defined as major maternal morbidity by local researchers).
- Maternal mortality
- Prolonged maternal admission. Admission in days measured from delivery of the child.
- Diagnosis during admission: endometritis, suspected infection, UTI treated with antibiotics, wound infection treated with antibiotics, obstructed bowel disease, pneumonia, trombo-embolic complications, hypertensive disorders, postpartum haemorrhage, post caesarean, pre-eclampisa/HELLP, admission due to condition child, other.

Maternal parameters

- pain scores, measured hourly from start of labor using a VAS scale
- pain appreciation scores, measured hourly from the start of labor and after start of pain relief every 15 min in the first hour and hourly after that on a VAS scale.
- satisfaction with pain, measured on a scale of 0-10 after delivery
- side effects, during administration of pain relief
  - hypotension (systolic blood pressure <90 mmHg of <25% below baseline)
  - nausea/vomiting (none, mild, moderate, severe)
  - itching (none, mild, moderate, severe)
  - respiratory depression (respiratory rate <8/min)maternal fever during labor (temperature >38°C)

Neonatal outcome

- Apgar scores ≤ 6 after 1 and 5 minutes
- Umbilical cord pH < 7.10
- Admissions to the neonatal ward
- Diagnosis during admission: neonatal meningitis/neonatal sepsis (suspected or proven with culture), prematurity, IUGR, hypoglycaemia, glucose control, IRDS, chronic lung disease, meconium aspiration, pneumothorax/mediastinum, apnea, necrotizing enterocolitis, asphyxia (pH umbilical atrey <7.0 and/or Apgar score 1 min 0-3), intraventricular haemorrhage, periventricular leukomalacia, observation due to maternal medication, admission due to condition mother, other.

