# STUDY DESIGN

Multicentre non-blinded randomized controlled clinical trial. Time schedule will be 36 months, 3 months for preparations, 27 months for inclusions and 6 months for data analysis and economic evaluations. The study will be embedded within the Dutch Obstetric Consortium, starting in 10 centers (university hospitals, teaching and non-teaching hospitals).

Counseling and obtaining informed consent of low risk pregnant women will be done by their own primary care midwives, supported by research nurses/midwives of the Dutch Obstetric Consortium.

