## Randomisation, blinding and treatment allocation

Randomization stratified for centre and parity will take place after informed consent. Randomization will be performed through a web-based database located in the central data collection unit in the AMC in Amsterdam. Women will be randomly allocated to receive epidural analgesia of remifentanil PCA when they request pain relief during labor. There will be no blinding, as this is not possible with these two treatment methods.

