## Data Safety Monitoring Board (DSMB)

The Data Safety Monitoring Committee of the Dutch Obstetrical Consortium has been approached to monitor the progress of the study and safety of participating women. This committee consists of prof. dr. [name] (clinical epidemiologist AMC), prof. dr. [name] (neonatologist AMC) and prof. dr. [name] (gynecologist LUMC)

Serious adverse events (SAE) will be reported directly to this committee.

The advice(s) of the DSMB will be notified upon receipt by the sponsor to the METC that approved the protocol. With this notification a statement will be included indicating whether the advice will be followed.

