# STATISTICAL ANALYSIS

## Descriptive statistics

- 1. Maternal age: continuous, quantitative
  2. ASA physical status: continuous, quantative (1-5)
  3. Body Mass Index: continuous, quantative
  4. Parity: categorical, quantitative: (nulliparous / multiparous)
  5. Previous cesarean delivery: categorical, quantitative (yes/no)
  6. Gestational age: continuous, quantitative
  7. Maternal origin: categorical, quantitative (Caucasian, Mediterranean, Creole, Asian)
  8. Educational level: categorical, quantitative
  9. Number of fetuses: categorical, quantitative (1-3)
  10. Fetal condition at time of request pain relief: categorical, quantitative (optimal, non reassuring, fetal tachycardia)
  11. Start of labor: categorical, quantitative (spontaneous/induction)
  12. Use of oxytocin: categorical, quantitative (yes/no)

Mode of delivery: categorical, quantitative (vaginal delivery, instrumental delivery,

cesarean section)

- 1. Indication for cesarean section/ instrumental delivery: categorical, quantitative Duration first stage of labor: continuous, quantitative
  2. Duration second stage of labor: continuous, quantitative
  3. Time from request to start of analgesia: continuous, quantitative
  4. Duration of analgesia: continuous, quantitative
  5. Conversion from epidural analgesia to RPCA: categorical, quantitative (yes/no)
  6. Conversion from RPCA to epidural analgesia: categorical, quantitative (yes/no)
  7. Type of medication used for epidural analgesia: categorical, quantitative
  8. Increases or decreases in bolus dose for RPCA: categorical, quantitative
  9. Maternal pain scores: continuous, quantitative (0-10)
  10. Maternal pain appreciation scores: continuous, quantitative (0-10)
  11. Maternal satisfaction with analgesia: continuous, quantitative (0-10)
  12. Maternal temperature: continuous, quantitative
  13. Start of intravenous broad spectrum antibiotics; quantitative (yes/no)
  14. Maternal saturation: continuous, quantitative
  15. Maternal respiratory depression: categorical, quantitative (yes/no)
  16. Oxygen administered: categorical, quantitative (yes/no)
  17. Maternal hypotension: categorical, quantitative (yes/no)
  18. Nausea/vomiting: categorical, quantitative (mild, moderate, severe)
  19. Itching: categorical, quantitative (mild, moderate, severe)
  20. Postpartum hemorrhage >1000 ml: categorical, quantitative (yes/no)
  21. Major maternal complication
  22. Post spinal headache: categorical, quantitative (yes/no)

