centre and parity. First, the epidural and remifentanil group will be compared. Relative risks and 95% confidence intervals will be calculated for the relevant outcome measures. Categorical variables will be tested with the Chi-square test or Fisher’s exact test. Continuous variables will be tested with the Mann-Whitney U test. Time to delivery will be assessed using Kaplan-Meier analysis. Pain scores will be analyzed separately. We will report on pain during labor (area under the curve and mean pain score), worst pain during labor, pain scores at request pain relief. The analysis will be repeated on a par protocol basis. Subsequently, planned subgroup analysis will be done for nulliparous versus parous women, previous caesarean section, preterm labor (32 to 34 weeks and 34-37 weeks) and term labor (37-42 weeks), spontaneous versus induced labor, maternal educational level, maternal age (under 35 years versus over 35 years), multiple pregnancy. We will then use decision analysis to evaluate which intervention strategy, ie epidural analgesia or remifentanil is preferred in women who need analgesia during labor.

The low risk women will be included and analyzed in a separate trial. In the Dutch system with midwifery care and home births, there might be a difference in expectation of women with regard to pain during labor.

To be able to convince both primary and secondary care providers, these groups will be analyzed separately.

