# ADMINISTRATIVE ASPECTS AND PUBLICATION

## Handling and storage of data and documents

Data will be collected using a website dedicated to studies in the Dutch consortium for obstetric studies. Data monitoring will be done by research nurses in each of the participating centers. A substantial part of these research nurses is already working for the abovementioned consortium.

Patients will all receive a trial number at randomization, Data handling will be done anonymously, with the patient code only available to the local investigator. All data will be stored in a secured database on a secured computer, to which only the investigators will have access.

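### Unblinded local researchers decide which "other" events are major maternal morbidity, so the secondary morbidity comparison is open to labelling bias if those events are counted in it

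*Protocol*

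**What the plan says.** Section 6.1.2 (Secondary study parameters/endpoints, maternal outcome) has a morbidity item with seven named conditions: post spinal headache, postpartum haemorrhage (over 1 litre or blood products given), and "uterine rupture, eclampsia, amniotic fluid embolism, myocardial infarction, admission to ICU". An eighth, open entry follows: "other (defined as major maternal morbidity by local researchers". Its only criterion is the view of the local researcher.

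Section 3 calls the trial a "Multicentre non-blinded randomized controlled clinical trial". Section 6.2 adds: "There will be no blinding, as this is not possible with these two treatment methods". Neither section exempts anyone who assesses outcomes.

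The variable list in section 8.1 contains "Major maternal complication", with no type, categories or components. Postpartum haemorrhage above 1000 ml and post spinal headache stand on either side of it as separate variables. For the analysis, section 8.1 says: "Relative risks and 95% confidence intervals will be calculated for the relevant outcome measures". It also plans a chi-square or Fisher's exact test for categorical variables.

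On data checking, section 10.1 says: "Data monitoring will be done by research nurses in each of the participating centers". The data safety monitoring board in section 7.4 is asked "to monitor the progress of the study and safety of participating women". Classifying outcomes is not among its stated tasks.

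**The concern.** Seven of the eight morbidity entries are named conditions. The eighth is settled after the event by people who know which analgesic method the woman was allocated. A researcher who distrusts one method may call a borderline event major in that arm, and one who favours it may not. Stratifying randomisation by centre does not remove labelling that differs between arms within a centre.

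The open entry also has real work to do. The study-specific serious adverse events in section 7.2 are ventilated respiratory failure, cardiopulmonary resuscitation, anaphylactic shock, meningitis and epidural haematoma. None is named in the maternal morbidity list of 6.1.2. Unless such an event leads to intensive care admission, "other" is its only way into the morbidity item. Some of these events relate closely to one method: section 5.3 gives respiratory depression as a known risk of remifentanil, and an epidural haematoma belongs to the epidural route. Events for which an arm difference is most plausible are therefore among those left to discretion.

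At stake is the reading of a secondary safety comparison. A difference, or the lack of one, could partly reflect labelling.

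**Working it through.** The protocol has no figure on this point to reproduce. The check is a reading of the sections, followed by an illustration on assumed rates.

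**Reading**

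1. *Who decides?* Local researchers (6.1.2).
2. *Do they know the arm?* Yes (3 and 6.2).
3. *Is there a later blinded or central check of the label?* None is described (7.4 and 10.1).
4. *Does the label reach the comparison between arms?* The protocol does not settle this. Section 8.1 never links its complication variable to the morbidity item in 6.1.2, and it words the two differently. Three readings are possible:
   - all entries are pooled into the variable;
   - the variable holds only what remains after haemorrhage and headache;
   - each entry is reported on its own line.

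   The "other" events are exposed under all three, but the share of the compared count that they can move differs.

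**Illustration: inputs**

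- 1136 women randomised, of whom 568 (half) are expected to need treatment (section 4.4). With 1:1 allocation, which is assumed, this gives 568 randomised or 284 treated per arm.
- The true morbidity rate is not in the protocol. It is assumed equal in both arms, at 2%, 5% or 8%.
- *k* extra "other" labels are placed in one arm only.

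**Formulas.** With *a* true events among *n* women per arm:

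- RR = (a + k)/a
- SE(log RR) = √[1/(a+k) − 1/n + 1/a − 1/n]
- 95% CI = RR × exp(±1.96 × SE)

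**Example.** With n = 284 and 2%, a = 6. For k = 3, RR = 9/6 = 1.50, SE = √(1/9 − 1/284 + 1/6 − 1/284) = 0.52, and the CI is 0.54 to 4.16. For k = 6, RR = 2.00 (0.76 to 5.26).

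**Smallest k at which the interval excludes 1**

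| n per arm | assumed rate | a | k | RR | lower limit |
|---|---|---|---|---|---|
| 284 | 2% | 6 | 10 | 2.67 | 1.06 |
| 284 | 5% | 14 | 13 | 1.93 | 1.03 |
| 284 | 8% | 23 | 15 | 1.65 | 1.01 |
| 568 | 2% | 11 | 12 | 2.09 | 1.03 |
| 568 | 5% | 28 | 17 | 1.61 | 1.02 |
| 568 | 8% | 45 | 20 | 1.44 | 1.01 |

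**Chance of a false significant difference.** This uses a normal approximation for two proportions, two-sided 5%, with a true rate of 6% assumed in both arms. The chance is about Φ(d/SE − 1.96), where d is the rate added in one arm and SE = √[p₁(1−p₁)/n + p₂(1−p₂)/n]. For n = 568 and d = 0.02, SE = √[(0.06×0.94 + 0.08×0.92)/568] = 0.0151, so d/SE = 1.32 and Φ(−0.64) = 0.26.

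| d (points) | RR | labels if n = 568 (568 × d) | chance, n = 568 | chance, n = 284 |
|---|---|---|---|---|
| 1.5 | 1.25 | about 9 | 0.17 | 0.11 |
| 2 | 1.33 | about 11 | 0.26 | 0.15 |
| 3 | 1.50 | about 17 | 0.48 | 0.27 |

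Against about 34 true events (568 × 0.06), 9 to 17 added labels would raise that arm's count by 25% to 50%.

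**The case against.** The strongest reply is that pooling is inferred. The list in section 8.1 stands under descriptive statistics, and its complication variable is not tied to 6.1.2. Haemorrhage and post spinal headache are listed apart from it, so the variable may hold only the rarer remainder. That stands. A reader might infer that the protocol tests a composite containing the self-labelled events and that its false-positive rate rises to 17%, 26% or 48%. The protocol does not support this: it states no pooling and gives no rate, and the 6% behind those percentages is an assumption. They also require 9 to 17 one-sided labels outside every named condition, which nothing in the text suggests will occur.

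Second, an open category guards against missing unforeseen harm, and deleting it would do damage. That stands too. Comparing only the conditions named in 6.1.2 would keep post spinal headache and drop the serious events that section 7.2 itself singles out, unless they led to intensive care.

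Third, a truly major event would normally also be a serious adverse event and go directly to the safety board, and mortality, length of stay and admission diagnoses are recorded separately. This gives a record against which labels could be checked. It is a partial safeguard, since no section says that such a check will be made or ties "other" to the serious adverse event definition.

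Last, details of this kind are often left to a statistical analysis plan. That covers how the entries are combined. It does not cover the rule that local researchers define the event, which the protocol itself sets.

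**Conclusion.** The point holds in limited form. The protocol gives the definition of one morbidity entry to people who know the allocation, describes no blinded classification, and carries an undefined complication variable into section 8.1. If "other" events are counted in that variable, or compared on their own line, the comparison is open to labelling bias in either direction.

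The size cannot be derived from the protocol. Under the assumed rates and 1:1 allocation, a few labels move the estimate, most of all at low rates, and 10 to 20 one-sided labels are needed before the interval excludes 1. This is an opportunity for bias and no evidence that bias occurs. It concerns one entry of a secondary outcome. Pain appreciation, the equivalence conclusion and the sample size are untouched.

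**What to change.** In sections 6.1.2 and 8.1, define the compared major-morbidity variable as the conditions already named in 6.1.2 plus the study-specific serious adverse events already named in 7.2. Report the remaining locally labelled "other" events separately by arm, each with a short description, and add a sensitivity analysis that includes them in the count.

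The change is a few sentences, made before outcomes are known. Data collection need not change if the case report form already records the type of event. The downside is that an unforeseen serious event on neither list is counted only in the sensitivity analysis, the listing and the serious adverse event report.

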## Study procedures

Women will be asked to participate in this study before active labor has started, preferably during antenatal consult in the third trimester. They will be randomized and allocated to one of the treatment groups. If they request pain relief during labor they will be treated according to randomization with:

1. Remifentanil patient controlled analgesia; 30 microgram boluses, lockout time 3 minutes, maximum dose limit 1200 microgram/hour. Possibility of increasing or decreasing the bolus dose. When indicated EA is available.

2. Epidural analgesia; according to local protocol. When indicated RPCA is available.

There will be no additional invasive tests performed. Maternal vital parameters (temperature, heart rate, blood pressure, respiratory rate and pulse oxymetry) will be monitored non invasively at regular intervals. In the first hour after starting pain relief these parameters will be monitored with intervals of no longer than 15 minutes, after that with intervals of no longer than 1 hour. Maternal pulse oxymetry will also be monitored continuously.

Fetal heart rate and uterine activity will be measured continuously by external monitoring. When data are difficult to interpret or complications (such as meconium stained amniotic fluid, failure to progress in labor) occur, invasive monitoring by means of scalp electrode and intra-uterine pressure recording can be instituted.

Observations for known side effects will be made; respiratory depression, hypotension, nausea/vomiting and itching. Side effects will be managed by established local protocols.

Hypotension (systolic blood pressure < 90 mmHg or > 25% below baseline) will be treated with intravenous fluids, ephedrine 5 mg i.v. or phenylephrine 0.1 mg i.v. When oxygen saturation drops below 92% oxygen will be given.

Maternal pain score and pain appreciation score will be assessed using a visual analogue scale (VAS) ranging from 0-10. Women will be asked to mark the level of pain experienced during a contraction every hour starting at admission in the delivery room. Pain appreciation scores will be asked every hour, participating women will be asked to mark their level of satisfaction with analgesia. This will also be assessed using the visual analogue scale ranging from 0-10. After delivery an overall satisfaction score with pain(0-10) will be asked. Patient satisfaction will also be assessed by HADS and WDQ.

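### Hypotension is defined with opposite signs on the 25% limb in Protocol 6.1.2 and 6.3; the 6.1.2 outcome line should be corrected to match 6.3 (minor)

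*Protocol*

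**What the plan says.** Protocol section 6.1.2 (Secondary study parameters/endpoints) lists the side effects recorded during pain relief. Its entry for hypotension reads "hypotension (systolic blood pressure <90 mmHg of <25% below baseline".

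Section 6.3 (Study procedures) names hypotension among the side effects to be watched for ("Observations for known side effects will be made; respiratory depression, hypotension, nausea/vomiting and itching"). Shortly afterwards it gives a threshold as part of a treatment instruction: "Hypotension (systolic blood pressure < 90 mmHg or > 25% below baseline) will be treated with intravenous fluids", with vasopressors as alternatives.

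The variable list in section 8.1 carries the item only as "Maternal hypotension: categorical, quantitative (yes/no". That is normal for such a list, but it does not settle which threshold applies. Section 8.1 also plans that "Relative risks and 95% confidence intervals will be calculated for the relevant outcome measures".

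**The concern.** The two sections name the same condition with the same absolute limb (below 90 mmHg) and the same percentage, but the inequality on the relative limb points in opposite directions. Section 6.1.2 is where someone building the case report form or coding the outcome would look first, and it is the version that makes no clinical sense when read literally.

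Hypotension is one of the side effects on which the two arms may be expected to differ. Section 5.3 states: "Known risks of epidural analgesia are hypotension, increased use of oxytocin and increased risk of instrumental delivery". Maternal side effects are a secondary objective in section 2. Section 6.3 requires blood pressure at intervals of no more than 15 minutes in the first hour of pain relief and no more than one hour after that. With repeated readings, a rule that any fall of less than 25% satisfies would be met by many women in both arms. As both event proportions rise towards 1, their ratio moves towards 1, and a real difference between the arms could be hidden.

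**Working it through.** No figure in the plan needs reproducing. The check sets the two printed rules side by side and works out which readings they classify differently.

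**Inputs.** The 90 mmHg limb and the 25% figure come from Protocol 6.1.2 and 6.3. The protocol gives no baseline pressures, so the baselines below are assumed for illustration. Write B for baseline systolic pressure and S for a later reading, both in whole mmHg.

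**Rules.**
- Section 6.3: event if S < 90 or S < 0.75 × B.
- Section 6.1.2 taken literally, with the printed *of* read as *or*: event if S < 90 or the fall is under 25%, that is, 0.75 × B < S < B.

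**Crossover.** The two limbs of the 6.3 rule coincide where 0.75 × B = 90, so B = 90/0.75 = 120 mmHg. At baselines up to 120, any fall of more than 25% already takes the reading below 90. The literal 6.1.2 rule then misses nothing and errs only by counting small falls. Above 120 it also misses events.

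| Assumed B | 0.75 × B | Counted by literal 6.1.2 but not by 6.3 | Counted by 6.3 but missed by literal 6.1.2 |
|---|---|---|---|
| 100 | 75 | 90 to 99 | none |
| 120 | 90 | 91 to 119 | none |
| 130 | 97.5 | 98 to 129 | 90 to 97 |
| 140 | 105 | 106 to 139 | 90 to 104 |

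**Two single readings.**
- B = 120, S = 115: the fall is 5/120 = 4.2%. Literal 6.1.2 calls this hypotension; 6.3 does not.
- B = 140, S = 100: the fall is 40/140 = 28.6%. Section 6.3 calls this hypotension and requires treatment. Under literal 6.1.2 it meets neither limb, since 100 is not below 90 and 28.6% is not under 25%.

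A rule that accepts the first reading and rejects the second cannot be what was meant. The 6.3 rule is coherent and gives the intended direction.

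**The case against.** The strongest reply is that the two sections may not conflict at all. In 6.1.2 the subject of both limbs is systolic pressure, so the second less-than sign can be read like the first: pressure below the level that lies 25% under baseline. That is S < 0.75 × B, which is the 6.3 rule. On this view the line is awkward shorthand. It can be added that nobody would code a fall of a few mmHg as hypotension, that 6.3 gives staff an unambiguous rule, that no effect on the trial's results has been shown, and that this is one of several secondary side effects.

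Most of this stands. The shorthand reading is possible, 6.3 does recover the intent, and no size of effect can be claimed. These points are why the matter is minor. They do not make the printed line right. It needs a charitable reading to agree with 6.3, it also has *of* where *or* is meant, and it is the only outcome definition of hypotension in the protocol. The 6.3 wording is attached to a treatment instruction, so an analyst working from the endpoint section would not necessarily turn to it.

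**Conclusion.** The inconsistency is real and minor. The outcome line in 6.1.2 is wrong as printed, and 6.3 shows what was intended. If 6.1.2 were followed literally, small falls would be counted at every baseline, and falls of more than 25% that stay at or above 90 mmHg would be missed at baselines above 120 mmHg. The reading ranges follow from the two printed thresholds; only the baselines are assumed.

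The effect on event rates or on the relative risk cannot be quantified from the protocol. The shift of the ratio towards 1 would arise only if the literal wording reached the case report form or the coding. The primary endpoint, the sample size and the treatment of hypotension are not affected, and anyone working from 6.3 would use the right definition.

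**What to change.** In section 6.1.2, replace the hypotension entry with: systolic pressure below 90 mmHg, or more than 25% below baseline. This corrects both the sign and the *of*/*or* slip and brings the entry into line with 6.3. Then confirm that the case report form and the analysis coding use this definition.

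The cost is one corrected line and one check. Treatment, the data collected and the sample size do not change.
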